## Abstract

**Background:**

Gut microbiota may influence brain functions. Therefore, we prepared a study protocol for a double-blind, crossover, randomized clinical trial to determine the complex effects of human probiotics on memory, psychological, and biological measures in the elderly.

**Methods:**

We selected eligible participants using an effective electronic questionnaire containing the inclusion and exclusion criteria and a brief electronic cognitive test. One-third of the respondents with the worst cognitive scores on the electronic test are randomized to group A, starting with a 3-month probiotic intervention, and to group B, starting with a placebo. In a crossover design, both groups change their intervention/placebo status after 3 months for the next 3 months. Participants refusing longer personal assessments due to the COVID-19 pandemic were randomly allocated to one of two subgroups assessed online. Participants in both groups are matched in age, education, gender, and cognitive scores on electronic testing at baseline. At three time points, participants are assessed using a neuropsychological battery, self-report measures of mood, a physical fitness test, blood, urine, and stool samples, and actigraphy. A subset of participants also provided their biological samples and underwent the neuropsychological battery in an extended testing phase 3 months after study termination to find out the long-term effect of the intervention.

**Discussion:**

This is the first trial to address the comprehensive effects of human probiotics on memory and many other measures in the elderly. We assume that the probiotic group will have better outcomes than the placebo group after the first and second trimesters. We expect that the probiotic effect will persist for the next 3 months. These study’s findings will contribute to an interesting area of how to improve memory, psychological and biological and other factors naturally and will examine the importance of probiotics for overall health in the elderly.

**Clinical trial registration:**

[clinicaltrials.gov], identifier [NCT05051501].

## Introduction

The aging population may be associated with the worsening of memory and mood. Natural ways are sought to compensate for such impairments. One of the proposed options to achieve this is to modify the composition of gut microbiota and their by-products. This may be a surprising yet highly promising way to influence brain function and blood composition (Wilmanski et al., 2021; Wu et al., 2021; Li et al., 2022).

The gut microbiota is a vast bacterial community living in a symbiotic relationship with a human host. Neural, hormonal, and immunological signaling between the host and the microbiome occurs through the microbiota-gut-brain axis system (Collins et al., 2012; Wu et al., 2021; Li et al., 2022). The bidirectional nature of this communication axis has recently raised the question of whether memory impairment could be influenced by bolstering the gut microbiome.

The effects of microbiome interventions on changes in brain chemistry and cognition are a flourishing field within animal modeling (Desbonnet et al., 2008, 2010; Bercik et al., 2010). Notably, a recent study found that transplanting microbiota from young mice into older mice also attenuated aging-related cognitive impairment (Boehme et al., 2021). The intestinal microbiota in humans can have various effects on the brain (Collins et al., 2012). Gastrointestinal diseases, such as irritable bowel syndrome, commonly have psychiatric comorbidities (Wu, 2012). A clinical trial reported an increase in the mean Mini-Mental State Examination score by 1.9 points in patients with Alzheimer’s disease following a 12 weeks administration of probiotic supplements. The probiotic treatment had a favorable effect on some blood biomarkers (malondialdehyde, high sensitivity C-reactive protein, markers of insulin metabolism, and triglyceride levels) but not on other markers of oxidative stress and inflammation (Akbari et al., 2016).

The precise mechanisms through which microbiota can influence cognition and mood are not yet well-understood, with most evidence coming from animal models (Eastwood et al., 2021). Probiotics may affect brain function by influencing brain chemistry and neurotransmitter production (Eastwood et al., 2021; Salami, 2021). Bravo et al. (2011) have shown that probiotic supplementation in mice led to an altered expression of GABA receptors and also reduced anxious and depressive behavior. This effect was, however, only seen in mice with an intact vagus nerve (Bravo et al., 2011), suggesting that neural pathways also play a role in gut–brain communication. The gut microbiota can also influence brain function *via* immunological pathways. For example, the probiotic strains *Bifidobacteria* and *Lactobacilli* have been shown to reduce the production of proinflammatory cytokines (Desbonnet et al., 2008, 2010; Rodrigues et al., 2012) and increase the production of anti-inflammatory cytokines (Rodrigues et al., 2012). This may improve the blood-brain-barrier integrity and prevent bacterial translocation (Eastwood et al., 2021; Salami, 2021). In a study, administration of probiotics from strain Lactobacilli had a positive effect on memory performance in aged mice and, at the same time, reduced levels of inflammatory cytokines and increased the production of anti-inflammatory cytokines (Huang et al., 2018). Probiotics can also decrease oxidants and increase antioxidants (Salami, 2021). In a clinical trial with Alzheimer’s disease (AD) patients, Akbari et al. (2016) found that probiotic treatment decreased oxidant malondialdehyde and the inflammatory protein marker, high-sensitivity C-reactive protein. This was associated with an improved score on a memory test following the probiotic treatment.

Probiotics may be a promising option for improving common symptoms of several brain and psychiatric diseases. While the gut microbiota has been of great interest in animal models in recent years, evidence for its effect on memory, mood, or movement in humans is still scarce, as summarized by several recent reviews (Li et al., 2021; Salami, 2021; Klann et al., 2022; Mukilan, 2022; Xiang et al., 2022) or described in original papers (Marotta et al., 2019; Handajani et al., 2022). A probiotic supplement is responsible for memory retrieval in the case of memory impairment. Therefore, it could be of potential use in the treatment of neurodegenerative disorders such as mild cognitive impairment or Alzheimer’s disease (Mukilan, 2022). The interplay of gut microbiota and cognition has been the focus of recent research. Increasing evidence suggests that a healthy gut microbiota is crucial for normal cognitive processing. Some studies have focused on the effects of either gut microbiota or probiotic bacteria on the brain’s cognitive function in health and disease status (Salami, 2021). Indeed, the administration of tempeh-derived probiotics increased the cognitive domains of memory, language, and visuospatial function (Handajani et al., 2022). A study by Marotta et al. (2019) showed an improvement in depressive mood state, anger, and fatigue and improved sleep quality in the group using probiotics, while no between-group differences were found (Marotta et al., 2019).

A recent review summarized pre- and probiotic studies related to Parkinson’s disease in humans (Klann et al., 2022). They found out that human clinical trials investigating probiotic supplementation for treating or managing Parkinson’s disease are limited. Probiotics are thought to improve symptoms by altering the gut microbiota composition to reverse dysbiosis and disrupt inflammation-related pathways (Klann et al., 2022).

In the current paper, we introduce a randomized clinical trial protocol exploring the effects of novel probiotics from human supplements on memory, psychological and biochemical measures in older adults with normal cognitive performance and mild cognitive impairment. The study uses human probiotic supplements to see whether a 3-month treatment will improve selected measures in elderly participants. We extend previous research in several aspects. Our probiotics are obtained from the human microbiota. Currently, the vast majority of probiotic preparations come from beef cattle and are primarily used in the dairy industry. However, strains of bacteria from cattle and humans differ in many aspects. We use a randomized, double-blind, placebo-controlled clinical trial with a crossover design whereby participant groups both receive the treatment and the placebo but in the opposite order. This will allow us to compare outcomes both within and between groups. Additionally, in contrast to previously published literature, we (a) used multiple validated cognitive measures to monitor the treatment’s effect on cognition, (b) used various psychological and related aspects to evaluate the effect of the probiotic treatment on mood, (c) used multiple types of biological samples involving blood, urine, and stool samples to trace the effect of the treatment on biological measures, and (d) will explore a short-term effect of probiotics by repeated examinations 3 months after the study termination.

## Participants and methods

Our study was carried out at two centers: (1) the University Hospital Kralovske Vinohrady (UHKV), Charles University, Third Faculty of Medicine, Prague, and (2) the National Institute of Mental Health (NIMH) in Klecany near Prague, the Czech Republic, from January 2021 to May 2022. All the participants signed informed consent. The study was approved by the Ethics Committees of NIMH Klecany in 2020 (No 78 and 165/20) and UHKV Prague in 2020 (No EK-VP 17/0 and 1/2020). The study was registered on the clinicaltrials.gov portal with registration number NCT05051501.

### Inclusion and exclusion criteria of eligibility for the study

The inclusion criteria included age between 55 and 80 years, Czech as a native language, preservation of daily life activities within the community, and good sight and hearing.

Participants were excluded from the study if they had had any of the following diseases or conditions currently or in the past: a disease of the digestive tract (celiac disease, Crohn’s disease, etc.), a neurological disease of the brain (epilepsy, major head injury, stroke, brain operation, brain tumor, etc.), psychiatric disease or treatment (schizophrenia, bipolar disorder, drug addiction, alcoholism, etc.), organ failure (heart, kidney, etc.), an oncological disease in the last 5 years or were after chemotherapy or radiotherapy, an immune-mediated disease, an operation in general anesthesia in the previous 3 months, use of cognitive enhancers, and use of antibiotics or other probiotic supplements 3 months before the start of the study. Depression was not an exclusion criterion.

### Participant recruitment and allocation

We correctly expected that identifying appropriate people with many criteria would be difficult. Therefore, we chose a cost-effective way of recruitment using an electronic questionnaire with all the inclusion and exclusion criteria. People were invited to complete the electronic questionnaire *via* massive electronic advertisements on senior websites, local newspapers, and magazines, on television, on the radio, in newsletters, and advertisements distributed by the employers of investigators. Another source was contact databases from our previous projects (Bartos and Raisova, 2016; Bartos and Fayette, 2018; Bartos et al., 2020).

The second and major reason for electronic recruitment was an attempt to remotely assess episodic short-term memory and to choose those participants with mild memory impairment. Therefore, we have developed an electronic memory test with the abbreviation ALBAV (Bartos and Krejcova, 2022). The principles of this electronic examination were derived and modified from two validated tests for a brief cognitive evaluation in person, i.e., the Amnesia Light and Brief Assessment (ALBA) and the PICture Naming and Immediate Recall (PICNIR), introduced in the Czech neurological journal (Bartos, 2016, 2018, 2019; Bartos and Diondet, 2020). They were used in case reports on two patients with dementia and their adult children in English (Bartos, 2021).

Fully self-administered testing via the Internet consisted of three memory subtests. First, participants were asked to write down one correct name in ten consecutive black and white pictures. Then they wrote them down again in any order immediately after naming them. A number of correctly recalled picture names were recorded. Secondly, they were asked to copy and memorize a sentence of ten words. Almost every word belonged to a different grammatical case in the Czech language. Only delayed recall of correct words in the sentence was scored. Participants completed the third task between sentence encoding and delayed recall. They were instructed to carry out ten simple gestures described as infinitive verbs by one word on the screen. Participants were not instructed to memorize these gestures. After they had demonstrated all the gestures, they were asked to write down as many of the gesture verbs in any order as they could recall. The total score of the ALBAV was calculated as a sum of correctly recalled names of pictures, sentence words, and gestures, each with a 10-point maximum. Thus, the score ranged from 0 to 30 points. We invited only those individuals with possible memory impairment, as measured by ALBAV scores ≤20 points, to participate in our clinical trial. The purpose of these procedures was to effectively recruit potential participants with mild memory impairment and not cognitively normal individuals (it made no sense to improve their normal memory) and not patients with dementia (they were excluded with the inclusion criterion of preserved activities of daily living as stated in section “Inclusion and exclusion criteria of eligibility for the study”).

The recruitment of participants is displayed in Figure 1. Hundreds of individuals completed the electronic questionnaire. Of those, 492 fulfilled all the criteria for participation in our study. Choosing only those participants with possible memory impairment using an ALBAV score ≤ 20 resulted in a further reduction of eligible participants to 136. The resulting number of participants represented 28% of the total, with the worst memory performance of the group that filled out the electronic recruitment questionnaire and the electronic memory test ALBAV and fulfilled all the criteria (*n* = 492). A final group of 91 participants was divided into two subgroups. A small subgroup (*n* = 19) of participants feared the COVID-19 infection during the pandemic. Thus, they were assessed with cognitive tests remotely *via* computers using monitors, web cameras, speakers, and microphones. Our experinces with distant testing were described recently (Polanska and Bartos, 2022). The rest of the procedures included completing self-report questionnaires, physical condition tests, and sample collection in person. All procedures were performed in person on the remaining 72 individuals.

**FIGURE 1 F1:**
[figure not shown]
Participant recruitment and allocation flowchart.

### Trial design

Our study was a randomized, double-blind, placebo-controlled trial with a crossover change of probiotics and placebo, which is shown in Figure 2.

**FIGURE 2 F2:**
[figure not shown]
A cross-over design of the clinical trial with probiotics. T1 denotes the time of first visit when participants were assessed with the PROCOG cognitive battery. The two groups received both probiotic and placebo tablets but in a reverse order. At T2 the participants brought back baseline urine and stool samples and their blood was collected. They also got the first set of probiotic/placebo tablets. All examinations and procedures from T1 and T2 were repeated at T3 when the participants got the second set of probiotic/placebo tablets. All examinations and procedures similar to T3 were repeated at T4 and T5.

All 91 participants were divided into two subgroups based on the order in which they completed the electronic registration form. One subgroup included participants with odd position numbers; the other one had even numbers. After checking for statistically significant sociodemographic differences between two subgroups, a few individuals were exchanged between these subgroups. This ensured that both subgroups matched in age, education, gender, and ALBAV scores before the start of the trial. Unexpectedly, 19 participants did not wish to come for testing in person due to the COVID-19 pandemic. Therefore, they were transferred from in-person to online assessment. These individuals were removed from the original allocation to online subgroups of participants.

A crossover design did not strictly confine one group of individuals to an intervention or placebo. Each group received both placebo and probiotics in tandem for 3 months each, but in reverse order. Members of group A start with a 3-month use of probiotics and continue with a 3-month use of placebo. The order of tablets is reversed for group B. There was no washout period between treatments.

Both participants and administrators were blinded to the type and order of intervention and placebo.

Each participant was evaluated during four visits at the University Hospital Kralovske Vinohrady, Prague, or the National Institute of Mental Health, Klecany, Czech Republic. A subset of the participants agreed with the last follow-up visit (*n* = 16 in group A, *n* = 18 in group B). They continued the study for a further 3 months without any intervention after the study termination to see the long-term effect of microbiome changes. Therefore, they had the fifth visit in addition. The first, third, fourth, and fifth visits were planned at 3-month intervals with a tolerance of ±1 week. The second visit was added 1 week after the first one to let participants take test tubes and bring back baseline stool and urine samples.

All measures were included at each visit except the first two. For logistical reasons, all procedures were divided into two visits at the beginning of the trial. Participants were administered a cognitive battery, completed self-report measures, and received test tubes to collect stool and urine samples during the first visit. The second visit included a physical fitness evaluation and sample collection. Participants also received either probiotic or placebo tablets and fiber or placebo fiber tablets for the next 3 months. A detailed description of each visit is described in Supplementary material 1.

Whenever possible, the administration of cognitive tests was conducted by the same administrator for individual participants throughout the whole period of the study until the fourth visit. Only two administrators performed cognitive testing on the fifth visit to each institution.

The participants received 3,000 Czech crowns for their participation at the end of the study (i.e., the fourth visit), which is equal to 123 EUR or 140 USD at the current currency exchange.

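### The main allocation is odd/even alternation followed by manual exchanges, so the trial is quasi-randomised and its between-group t-tests lack a randomisation basis and ignore the matched variables

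*Protocol article*

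**What the plan says.** The label is consistent. The Abstract (Background and Methods), the last paragraph of the Introduction and the opening of Trial design all present a randomized trial. Trial design states: "Our study was a randomized, double-blind, placebo-controlled trial with a crossover change of probiotics and placebo". The Abstract's Methods add: "One-third of the respondents with the worst cognitive scores on the electronic test are randomized to group A".

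The mechanism comes later in Trial design, in three steps:

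- Split: "All 91 participants were divided into two subgroups based on the order in which they completed the electronic registration form". The rule was parity of position: "One subgroup included participants with odd position numbers; the other one had even numbers".
- Exchange: "After checking for statistically significant sociodemographic differences between two subgroups, a few individuals were exchanged between these subgroups". The section gives the result of this step as follows: "This ensured that both subgroups matched in age, education, gender, and ALBAV scores before the start of the trial".
- Transfer: 19 people who declined in-person testing were moved. On their place in the allocation, the section says: "These individuals were removed from the original allocation to online subgroups of participants".

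On those 19, the Abstract says: "Participants refusing longer personal assessments due to the COVID-19 pandemic were randomly allocated to one of two subgroups assessed online".

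Proposed analysis names an unpaired t-test between groups at each time point, or a paired t-test between time points. Cognitive outcomes are analysed separately for in-person and online participants; the other outcomes are pooled. The only further factor named is apolipoprotein E status.

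**The concern.** A position number fixes each person's group in advance, and a later exchange made on observed baseline values is a decision, not a draw. No random element is described for the main split. A t-test between groups formed this way relies on a modelling assumption that the groups are comparable. It cannot appeal to a randomisation distribution.

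Two things are at stake. Readers and later evidence syntheses will take the word randomized at face value and give the causal claims the weight it implies. Also, the variables used to force balance are absent from the test, so its standard error does not reflect how the groups were formed.

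The between-group comparison matters here despite the crossover. There is no washout, and the same Trail Making form is used at every session, so change within a person can mix treatment with practice. The other group is the control for that.

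**Working it through.** **1. Label against mechanism.**

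| Feature | Abstract, Introduction, opening of Trial design | Detailed account in Trial design |
|---|---|---|
| Main split of 91 | randomized | odd/even position in registration order |
| After the split | groups described as matched (Abstract) | a few people exchanged after significance checks |
| The 19 online | randomly allocated to two online subgroups (Abstract) | removed from the original allocation; method not given |

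The article does not say how the two subgroups became A and B. A random draw at that point would randomise one label for the whole cohort, not the participants.

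**2. The plan's own power figures.** Inputs from Power calculation: two-sided α = 0.05, power 0.80. I solved the noncentral t for d, with noncentrality d√(n₁n₂/(n₁+n₂)) for two samples and d√n for pairs. Group sizes are not in the text, so splits of 91 and 72 were tried.

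- Two-sample, 45/46: d = 0.594 (stated 0.59).
- Two-sample, 36/36: d = 0.670; 32/40: d = 0.674 (stated 0.67).
- Paired, n = 44: 0.432; n = 45: 0.427 (stated 0.43).
- Paired, n = 31, 32, 33: 0.520, 0.511, 0.503 (stated 0.51, so n = 32).

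All four figures reproduce; no arithmetic error is alleged. If 0.51 reflects allocated numbers, the in-person split is 32 and 72 − 32 = 40.

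**3. What significance-guided exchange does to the unadjusted test.** Assumptions: n = 91, four independent standard-normal covariates, no treatment effect, 10,000 runs per setting. The most imbalanced covariate is corrected by exchanging extreme people until all four p-values pass a threshold. The chance that at least one of four tests is significant at 0.05, which triggers an exchange, is 1 − 0.95⁴ = 0.185 (simulated 0.184).

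| Outcome variance explained by the four covariates | Unadjusted type I error, exchange until p ≥ 0.05 | Unadjusted type I error, exchange until p ≥ 0.5 |
|---|---|---|
| 0% | 0.050 | 0.052 |
| 30% | 0.045 | 0.022 |
| 60% | 0.038 | 0.006 |

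The covariate-adjusted test stayed between 0.049 and 0.053 throughout. The Monte Carlo standard error near 0.05 is √(0.05 × 0.95/10,000) = 0.002.

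**4. What adjustment could gain.** If the covariates explain a share R² of outcome variance, the adjusted detectable d is roughly 0.59 × √(1 − R²), ignoring the few degrees of freedom spent. That is 0.59 × √0.7 = 0.49 for R² = 0.3 and 0.59 × √0.4 = 0.37 for R² = 0.6. The document gives no R²; these values only show a range.

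**5. Which people were matched.** In the order the text gives, the match is made on 91 and the 19 then leave: 91 − 19 = 72. The in-person cognitive analysis uses the 72, and no balance check on them is described.

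**The case against.** The exchanges came before the trial started and aimed at four named variables, and participants and administrators were blinded. Alternation by registration order gives little room for selection if nobody knew which subgroup would start on probiotics. All of this stands and lowers the concern, but it does not make the allocation random. The text also does not say what the person making the exchanges knew.

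Several stronger readings are tempting and are not supported:

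- *The tests produce false positives.* If exchanges depended only on the named variables, the error runs the other way.
- *People were hand-picked to favour an arm.* No selection rule is given, so this would be inference.
- *The bias can be sized against the detectable 0.59.* A shift in an unmeasured factor is in SDs of that factor, while 0.59 is in SDs of the outcome. Dividing one by the other assumes a correlation of 1 and every exchange pushing the same way, and the number exchanged is not reported.
- *All the t-tests fail.* Within-group paired tests never rested on randomisation between arms, and stable differences between people cancel in them.
- *The two accounts of the 19 contradict each other.* They can be read together: removed, then allocated at random between two online subgroups. Trial design is silent on the method.
- *The implied 32/40 split shows imbalance.* It shows unequal numbers, not unequal covariates. Matching on 91 still applies to the pooled biochemical, self-report and fitness outcomes.

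An analysis plan that is not shown may hold an adjusted model. The article nevertheless names plain t-tests, and its label conflicts with the mechanism it describes itself.

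**Conclusion.** The point holds for the label and for the between-group comparisons. The 91 were allocated by deterministic alternation and then manual matching, so the design is quasi-randomised and causal claims should be limited to match. The unadjusted between-group test ignores the variables used for matching.

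If exchanges followed only those variables, the result is a conservative test and lost power. Under the simulation's assumptions, type I error ranged from the nominal 0.05, when the variables are unrelated to the outcome, down to 0.006, when they explain 60% of its variance and balancing is tight. If the choice of whom to exchange was discretionary, bias in either direction is possible, and the document gives no basis for a figure. Balance in the 72 is unverified, which is not evidence that it is poor.

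**What to change.** - Replace the word randomized by *quasi-randomised (alternation by registration order, then manual matching)* in the Abstract (Background and Methods), the last paragraph of the Introduction and the opening of Trial design. Limit causal claims accordingly.
- Adjust the between-group comparisons for age, education, gender, ALBAV score and the outcome's baseline value. This restores calibration for the matched variables; it does not restore randomisation.
- Report how many people were exchanged and by what rule, and whether whoever did it knew the sequences.
- State how the 19 online participants received their sequence, so that the Abstract and Trial design agree.
- Tabulate the four matched variables by group in the 72.
- If the original positions were kept, add a sensitivity analysis by original odd/even position. It still rests on alternation, but it removes the effect of the exchanges.

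The cost is wording, one adjusted model, one balance table and possibly one sensitivity analysis, all from registration or baseline data. The downside is a less favourable design label and a little more analysis.

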### Power calculation

Given our sample size, we will able to detect the effect size of Cohen’s d = 0.43 in the matched-pairs two-tailed *t*-test, assuming power = 0.8 and α = 0.05. This will be d = 0.51 in those tests when only in-person data could be used.

For between-group comparisons, we could detect the effect size of Cohen’s d = 0.59 in a two-sample two-tailed *t*-test, assuming power = 0.8 and α = 0.05. This would be d = 0.67, assuming the use of only in-person data.

All power calculations were performed in G*Power 3.1.9.7 Software (Faul et al., 2007). As we did not attain equal group numbers, the sensitivity of the matched-pairs *t*-test is computed for the smaller group. This means we could detect a slightly smaller effect size for larger groups than reported here.

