**FIGURE 4 F4:**
[figure not shown]
Expected hypotheses of cross-sectional (inter-group) and longitudinal (intra-group) comparisons at different time points. We expect improvement following the 3-month administration of probiotics (Δ: H1a, H2b, H2, H3). We expect no favorable change following the 3-month administration of placebo (H1b: =, H2a: =/<). Finally, we expect group B ending with the probiotic arm will have better outcomes than group A ending with placebo arm at time point T5 because of different intervals from the probiotic use (6 months for group A and 3 months for group B).

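### The stated detectable effects carry no visit limit, but the T5 hypothesis rests on 16 versus 18 participants, where the detectable between-group difference is about d = 0.99

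*Protocol article*

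**What the plan says.** The Power calculation section gives its between-group sensitivity as "we could detect the effect size of Cohen’s d = 0.59 in a two-sample two-tailed *t*-test, assuming power = 0.8 and α = 0.05", and adds "This would be d = 0.67, assuming the use of only in-person data". For paired tests it says "we will able to detect the effect size of Cohen’s d = 0.43 in the matched-pairs two-tailed *t*-test" and "This will be d = 0.51 in those tests when only in-person data could be used". None of these statements is tied to particular visits.

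The Proposed analysis section plans an unpaired t-test at each time point and paired t-tests between time points. The Figure 4 legend, under Anticipated results and hypotheses, extends this to the last visit: "we expect group B ending with the probiotic arm will have better outcomes than group A ending with placebo arm at time point T5". The Abstract also expects the effect to last a further three months.

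The Trial design section gives the numbers at that visit: "A subset of the participants agreed with the last follow-up visit (*n* = 16 in group A, *n* = 18 in group B". The same section says that each participant kept the same test administrator, where possible, up to the fourth visit. For the visit after that it says "Only two administrators performed cognitive testing on the fifth visit to each institution". The neuropsychological battery section gives the RAVLT versions as one at T1, two at T3, three at T4 and one again at T5.

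**The concern.** A reader who takes the between-group sensitivity at face value will apply it to every planned between-group test, including the T5 hypothesis. That test has little more than a third of the participants, and they are the ones who agreed to an extra visit. The stated sensitivity is therefore not available for a comparison that the plan sets out as a prediction.

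The second issue is what a T4 to T5 change within a group could mean. By T5 both groups have taken probiotics, so no untreated group shows what time and repeated testing alone would do. For cognitive tests, the rater arrangement and the RAVLT form also change over that interval. A stable or falling score from T4 to T5 cannot by itself be assigned to persistence or loss of a probiotic effect.

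**Working it through.** **Inputs.** Total 91 and in-person 72 (Participant recruitment and allocation; Trial design). T5: 16 in A and 18 in B (Trial design). Two-tailed α = 0.05 and power 0.80 (Power calculation). The A/B split of the 91 and of the 72 is not in the text available, so several splits were tried.

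**Method.** Exact noncentral t, solved for d.
- Two-sample: noncentrality = d × √(n₁n₂/(n₁+n₂)), df = n₁+n₂−2.
- Paired: noncentrality = d × √n, df = n−1.

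**Step 1: reproduce the plan's figures.**

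| Comparison | n used | Detectable d | Stated |
|---|---|---|---|
| Between groups, all | 45/46 or 44/47 | 0.594 | 0.59 |
| Between groups, in person | 36/36 to 32/40 | 0.670 to 0.674 | 0.67 |
| Paired, all (smaller group) | 44 or 45 | 0.432 or 0.427 | 0.43 |
| Paired, in person (smaller group) | 32 | 0.511 | 0.51 |

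The stated figures are correct for samples of about 91 and 72.

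**Step 2: the same calculation at T5.**
- Between groups, 16 versus 18: √(16×18/34) = 2.910 and df = 32. Power of 0.80 needs a noncentrality of about 2.889, so d = 2.889/2.910 = 0.993.
- Ratio to the stated values: 0.993/0.59 = 1.68 and 0.993/0.67 = 1.48.
- Power at d = 0.59 (noncentrality 0.59 × 2.910 = 1.717) is 38%. Power at d = 0.67 (noncentrality 1.950) is 47%.
- Paired, ending at T5: d = 0.749 with n = 16 and 0.701 with n = 18. Power at the stated 0.43 is 36% and 41%. Power at the stated 0.51 is 48% and 53%.
- A one-sided test at 0.05 would still need d = 0.873. The plan's power statement is two-tailed.
- Share of participants contributing: 34/91 = 37%, leaving 57 who do not.

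**Step 3: what the T4 to T5 change can carry.** Group A took probiotics first and placebo second, and group B the reverse, so nobody is untreated at T5. Same-rater testing was kept, where possible, to the fourth visit, and two administrators per institution tested at the fifth. Seven raters had been trained. The RAVLT goes from version three to version one. The rater and form points concern cognitive tests only. Blood, urine, stool and questionnaire outcomes are not touched by them.

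**Step 4: which covariate suits the T5 contrast.** At T4 group B has just finished probiotics, so the T4 score already contains the effect whose persistence is in question. As an illustration, assume equal correlation r between T1, T4 and T5, no group difference at T1, and a difference δ present at T4 that persists fully at T5. Regressing T5 on T1 and T4 gives each a slope of r/(1+r). The adjusted difference is δ − δr/(1+r) = δ/(1+r), which is 0.63δ at r = 0.6, 0.56δ at r = 0.8 and 0.53δ at r = 0.9. Adjusting for T4 would understate a fully persistent effect by about 37% to 47%. Adjusting for the baseline value alone does not do this.

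**The case against.** The case on the other side has real force. The printed sensitivities contain no arithmetic error, and the article never attaches 0.59 to T5. It discloses 16 and 18 openly, presents T5 as an extension in a subset, and describes its approach in the Discussion as explorative. It nowhere calls T5 confirmatory. A reader might infer that the power figure is wrong, or that a confirmatory T5 test is claimed. The document supports neither.

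A reader might also infer that practice, test form and rater changes undermine the B-versus-A comparison. They largely do not. Both groups have had the same sessions, the same forms and the same T5 arrangement, and administrators were blinded. Raters would bias that contrast only if they were distributed differently by group, which nothing suggests. The lack of an untreated group does not defeat it either, because the hypothesis compares three with six months since probiotic use. The RAVLT form changes at every interval, and with three Czech versions a fourth session must reuse one. Nor does the text say that every participant met a new rater at T5: the two administrators per institution may be among the seven, and how many participants changed is not stated.

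Two things remain. The sensitivity statement is unqualified while the plan includes a T5 test and a directional T5 prediction to which it does not apply. Only the online results are labelled exploratory in the Proposed analysis section. The rater and form changes, with the absence of an untreated group, still limit the within-group T4 to T5 change.

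**Conclusion.** The point holds as a matter of scope. The stated sensitivities are right for the full and in-person samples and do not apply at T5, where the detectable between-group effect is about 0.99, some 1.5 to 1.7 times the stated values, and the detectable paired effect is 0.70 to 0.75. At the stated between-group effects, T5 power is 38% to 47%, so a non-significant T5 difference would be weak evidence of no difference. The article does not say that it would read such a result as equal persistence.

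The figures assume that all 34 contribute data. If any of them were tested online, which is not stated, cognitive comparisons by assessment mode would be weaker still. How the 34 differ from the other 57 is not given, so selection is a possibility and not a demonstrated bias. The limit on interpreting the T4 to T5 change applies within groups. It does not extend to the B-versus-A contrast.

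**What to change.** - In Power calculation, limit the present figures to T1–T4 and add those for T5: d of about 0.99 between groups, and 0.75 (A) and 0.70 (B) within groups.
- Label all T5 analyses exploratory.
- Base any T5 inference on the B-versus-A contrast adjusted for the baseline value (T1, or T2 for samples and physical fitness), and not for T4.
- Report the T4 to T5 within-group change descriptively only, noting the rater arrangement and the RAVLT form for cognitive tests.
- Compare T5 attenders with non-attenders on the data already collected at T1–T4.

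No new data are needed. The cost is a less favourable stated figure for T5 and a persistence claim that becomes exploratory.
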